### Analysis of primary outcome

The aim of the primary analysis is to examine the effectiveness of art psychotherapy in reducing the frequency and severity of aggressive incidences compared to usual care, as measured by the change in MOAS score from baseline to week 19 post-randomisation. The distribution of the MOAS scores will be assessed graphically using histograms and the mean (SD) or median [IQR] of the change in score from baseline to week 19 will be tabulated overall and by trial arm (art psychotherapy versus usual care). The change of primary outcome from baseline to week 19 will be assessed graphically using a scatter plot.

The primary outcome analysis will be performed on an ITT basis. Initially, we will use a linear mixed-effect regression model [27, 28], with the week-19 MOAS score as the dependent variable and the randomisation group as the independent variable, adjusted for the baseline MOAS score, random effect of the variable indexing strata based on gender and diagnosis of psychosis. In addition, we anticipate potential clustering in the intervention arm due to therapists. We will examine this by the ICC from the linear mixed-effect model and if there is a considerable amount of heterogeneity in the primary outcome associated with therapists, we will adjust the effect estimate for the partial clustering due to therapists. For this, both partially homoscedastic and heteroscedastic regression models will be explored, and we will report the results as appropriate. The homoscedastic model assumes between-cluster variability is only present in the intervention arm and the individual level variation is the same in both arms. The heteroscedastic model assumes between-cluster variability is only present in the intervention arm but allows different individual level variation in intervention and control arms [29, 30]. From the initial model(s), we will present the estimated difference in MOAS score at week-19 for the intervention group compared to the control group with 95% CI.

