## Methods

### Trial design

Full details of the SCHEMA trial design, setting, intervention, outcomes, and ethical approvals have been published in the protocol [12]. However, we provide a summary here as follows. The trial is a multicentre, two-arm, parallel-group, single-blind, individually randomised controlled trial (RCT) of effectiveness, comparing manualised interpersonal art psychotherapy to usual care. The RCT is being conducted in 8 NHS Trusts with secure care facilities and aims to recruit 150 participants (75 per trial arm). The total trial duration is 43 months with 20 months of recruitment. The end of the trial is defined as the last participant’s last visit [12].

The intervention arm is scheduled to receive 12 (1 h each) individual interpersonal art psychotherapy sessions, delivered by a trained HCPC registered art psychotherapist, plus usual care. Participants can receive up to 3 additional sessions throughout the trial for more personalised support, adjusting for the participant’s specific communication or therapeutic needs. The sessions cover the following 7 components: (1) personal goals, (2) coping responses and self-management, (3) relationships, (4) life events, (5) interpersonal themes, (6) imagined future and (7) final review. Participants will be considered as having completed the intervention if they complete at least 5 out of the 7 components listed above.

The control arm is scheduled to receive usual care, and participants are assessed and treated by specialist professionals. The multi-disciplinary team includes psychiatrists, clinical and forensic psychologists, mental health and ID nursing staff, and Allied Health Professionals. The team uses the Care Programme Approach to coordinate and plan participant care, including risk assessments, recovery-focused care and/or positive behaviour support [15]. Participants also have access to psychotherapy/psycho-educational work, specific offence-related treatment and pharmacotherapy treatment. Participants in the control arm are offered the art psychotherapy intervention at the end of their participation in the trial.

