### Randomisation

Participants were randomly allocated to receive either art psychotherapy plus usual care (UC) as the intervention arm, or UC with delayed art psychotherapy as the control arm. Participants were allocated to the intervention and control arm in a 1:1 ratio using randomly permuted blocks of 2, 4 and 6 created in Stata (version 17). This concealed allocation and minimised the predictability of the next allocation at the end of each block. Randomisation was stratified by sex and diagnosis of psychosis to achieve balance of baseline characteristics in the two groups.

The final randomisation list was generated by the senior statistician independently, keeping the trial statistician blind to the randomisation list. Randomisation took place online through the REDCap SCHEMA database and was available 24 h a day. Treatment allocations were automatically generated once the participant’s baseline data had been entered. As this is a single blind trial, the trial statistician, health economist and research support staff completing the primary outcome assessment are kept blind to allocation. For the statistical analysis, all data cleaning, manipulation, and analysis will be carried out by the trial statistician who will be kept blind to the arms allocation.

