### Sample size

The primary objective is to assess the effectiveness of art psychotherapy in reducing the frequency and severity of aggressive behavior in adult secure care as measured by the Modified Overt Aggression Scale (MOAS) [16]. Based on the results of the feasibility study [11], we assumed a minimum clinically important difference (MCID) of 5 points on the MOAS scale, a common standard deviation of 10 points in the control and intervention groups, and a correlation of 0.25 between the baseline and post-treatment MOAS scores. In addition, we may need to account for clustering by therapist, as a single therapist will apply the intervention to more than one patient. We assumed that each site would have a minimum of 2 therapists and the intraclass correlation (ICC) of the MOAS scores for the same therapist would be 1% in the intervention arm. Under these assumptions, 80% power and a type I error rate of 5%, 59 participants would be required in each arm. To account for an assumed attrition rate of 20%, this figure is inflated to a final sample size of 75 participants per arm, yielding a final sample size of 150 participants.

This would also allow the study to detect a change of 0.5 points on the Brief Symptom Inventory (BSI) Positive Symptom Distress Index (PSDI), used to evaluate changes in patient distress related to psychiatric symptoms [17]. Using an estimated SD of 0.8, the sample size calculated above would result in a power greater than 90% for the BSI comparison.

If the target recruitment (sample size) is not achieved, we will use sensitivity analysis with appropriate statistical methods as planned in the statistical analysis section. If the effect size (i.e. the mean difference of change in MOAS and its standard deviation) differs from our assumptions used in the sample size calculation, this may affect the power/sample size as shown in Table 1.

**Table 1 Tab1:** Potential effects of differing effect sizes and standard deviations on the sample size

Effect size	Power	SD	Method	Correlation (baseline and follow-up)	Alpha	Sample size (per arm)	Final sample size (inc. 20% dropout)
4	0.8	10	ANCOVA	0.25	0.05	92	230
6	0.8	10	ANCOVA	0.25	0.05	41	103
5	0.8	8	ANCOVA	0.25	0.05	37	93
5	0.8	12	ANCOVA	0.25	0.05	85	213

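### Therapist adjustment of the primary outcome hangs on an undefined ICC trigger, and without a site term that trigger and the therapist effect also pick up differences between Trusts

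*Protocol article*

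**What the plan says.** The Protocol article, under Analysis of primary outcome, starts from a linear mixed model for week-19 MOAS with arm, baseline MOAS and a random effect for the gender-by-psychosis strata. It then examines the therapist ICC: "if there is a considerable amount of heterogeneity in the primary outcome associated with therapists, we will adjust the effect estimate". For that adjustment, "both partially homoscedastic and heteroscedastic regression models will be explored, and we will report the results as appropriate". Both of these models place between-cluster variance in the intervention arm only. The section closes by saying that the estimate will come from the initial model or models.

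Under Sample size, a therapist ICC of 1% in the intervention arm and at least two therapists per site are already assumed. Under Analysis of secondary outcomes, the EQ-5D-3L, ReQoL-10 and BSI models include a therapist random effect with no condition attached. The repeated-measures ANCOVA of weekly MOAS names none.

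On site, the Trial design section states: "The RCT is being conducted in 8 NHS Trusts with secure care facilities". Site is not a stratification factor (Randomisation). It is also not a term in any model described under the primary, secondary, covariate, subgroup or economic analyses, and it appears only in the screening summaries.

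On blinding, the Randomisation section says that "all data cleaning, manipulation, and analysis will be carried out by the trial statistician who will be kept blind to the arms allocation".

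**The concern.** Three analyses can each become the primary result: no therapist term, the homoscedastic model or the heteroscedastic model. The choice follows a look at an ICC estimated from only a few patients per therapist, and the word *considerable* has no number behind it. The same plan treats therapist as a standing design feature for three secondary outcomes, but as optional for the primary one.

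The missing site term makes this worse. Patients of one therapist also share a Trust. Trust differences act in both arms, but the partial-clustering models allow correlation in the therapy arm only. Site variance is therefore read as therapist variance. That makes the trigger more likely to fire, and once it fires it widens the standard error of the treatment contrast although much of the site variation cancels between arms.

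Therapist identity exists in one arm only. Whoever fits the term can see which arm is which, at the very step where a discretionary model choice is made.

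**Working it through.** **Inputs from the Sample size section:** "minimum clinically important difference (MCID) of 5 points on the MOAS scale"; "a common standard deviation of 10 points in the control and intervention groups"; "a correlation of 0.25 between the baseline and post-treatment MOAS scores"; 80% power, 5% type I error, two-sided; therapist ICC 0.01 in the therapy arm; at least 2 therapists per site. With 8 Trusts that is at least 16 therapists.

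**Step 1. The plan's own figure.** n per arm = 2(z₀.₉₇₅ + z₀.₈₀)² × SD²(1 − r²)/Δ² = 2 × 7.849 × 100 × 0.9375/25 = 58.9, so 59 as stated. This contains no allowance for therapists. Adding it: m = 59/16 = 3.69; design effect = 1 + 2.69 × 0.01 = 1.027, in one arm only; n = 58.9 × (1 + 1.027)/2 = 59.7, so 60; 60/0.8 = 75 per arm. The total of 150 stands.

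**Step 2. Simulation set-up.** 8 equal sites, 2 therapists per site, 118 analysed, variance after baseline adjustment 100 × 0.9375 = 93.75, randomisation not stratified by site, strata effect negligible, REML with z-tests. Site ICC is an assumption, varied from 0 to 0.20. The 0.05 cut-off for the trigger is also an assumption, because the plan gives none.

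**Step 3. How the trigger behaves (true therapist ICC 0.01).**

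| Site ICC | Mean estimated therapist ICC | Estimate above 0.05 |
|---|---|---|
| 0 | 0.04 | about 30% |
| 0.05 | 0.07 | about 45% |
| 0.10 | 0.09 | 57-60% |
| 0.20 | 0.15 | 76-80% |

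The therapist effect is the same in every row; only the site variance changes. With a cut-off of 0.10 and no site variance, the trigger still fires in 17% of trials.

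**Step 4. Power for 5 points (therapist ICC 0.01).** Two sets of runs are shown, each as therapist-only against random site plus therapist.

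| Site ICC | First set | Second set | Mean SE (first set) |
|---|---|---|---|
| 0 | 78.8% / 78.8% | 79% / 79% | 1.84 / 1.82 |
| 0.05 | 77.7% / 80.1% | 79% / 80% | 1.87 / 1.81 |
| 0.10 | 73.7% / 77.6% | 74% / 78% | 1.89 / 1.78 |
| 0.20 | 73.5% / 83.8% | 72% / 81% | 1.98 / 1.69 |

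The loss is nil at 0, about 1-4 points at 0.05-0.10 and about 9-10 points at 0.20. The first set used 1,000 runs, so each power figure has a simulation error of about √(0.78 × 0.22/1000) = 1.3 points.

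**Step 5. Type I error.** At site ICC 0.20 the therapist-only model reports a mean SE of 1.98 when the estimate actually varies with SD 1.69, and it rejects a true null in about 2.5% of trials. With therapist clustering left unadjusted, the rate is about 5.4%, 6.3% and 7.4% at therapist ICC 0.01, 0.05 and 0.10. The two-stage rule itself gives about 5% at therapist ICC 0.01 and at most about 6% at 0.10. With z-tests, the site-plus-therapist model rejected in 4.5%, 7.4% and 3.4% of null trials at site ICC 0, 0.10 and 0.20 (simulation error about 0.7 points). These show no trend with site variance.

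**Step 6. Fixed or random site.** A fixed site effect also helps when sites differ (79.7% against 76.3% at site ICC 0.10; 82.2% against 71.8% at 0.20), but costs about 3 points when they do not. The random intercept cost nothing at site ICC 0.

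**The case against.** The strongest reply is that little is lost. The trigger looks at a nuisance parameter, not at the treatment effect, and the two-stage rule barely moves type I error. Randomisation was not stratified by site, so leaving site out does not bias the estimate. With two therapists per site, no therapist effect and 120 analysed, the initial model with neither term keeps 80.5% and 81.9% power at site ICC 0.05 and 0.10, within 1-2 points of a site-only model. The closing sentence of the section could also mean that the initial model is always reported. All of this stands except the last point: that sentence allows for more than one initial model, so it does not settle which result is primary. Nor can the gap be put down to condensation, since the article's Background says that it sets out the models and their covariates.

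Several stronger readings are tempting but unsupported:
- A reader might infer that power falls to about 67%. That needs one therapist per site, and the Sample size section assumes at least two. The nine therapists under Adherence describe a fidelity sample.
- A reader might call the trigger a coin toss. At the design ICC with no site variance it fires in about 30% of trials; it nears one half only if sites differ.
- A reader might say that every secondary model includes therapist. The weekly MOAS model does not.
- A reader might conclude that 150 is too few because 59 ignores clustering. Step 1 shows that it is not.

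**Conclusion.** The point holds as a defect of pre-specification with a modest, conditional cost. The primary model is not fixed, the trigger has no threshold, and the rule is at odds with three of the plan's own secondary models. Because no site term is described, the trigger and the therapist effect both respond to Trust differences. When they do, the result is conservative, not biased.

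The size rests on a site ICC that the documents do not give: no power loss at 0, about 1-4 points at 0.05-0.10, and about 9-10 points at 0.20 with type I error near 2.5%. Not adjusting errs the other way, with type I error about 7% if the true therapist ICC is 0.10. The figures assume equal sites, two therapists per site and a negligible strata effect.

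On blinding, a statistician who stays blind throughout cannot fit an arm-specific therapist term. That is a contradiction in the text. It does not show that any choice was, or would be, influenced by knowing the arms.

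**What to change.** Pre-specify one primary model: arm, baseline MOAS, the strata term, a random (not fixed) site intercept in both arms, and a therapist random effect in the therapy arm that is always fitted. Choose the residual-variance form in advance and use small-sample degrees of freedom such as Satterthwaite or Kenward-Roger, since there are only 8 sites and few patients per therapist. Report the model without therapist and the alternative variance form as sensitivity analyses, and delete the ICC trigger. Say whether the weekly MOAS model carries the same terms.

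Reconcile Randomisation with Analysis of primary outcome: state that the trial statistician is blind until the model code is locked, and that fitting the therapist term reveals the arms after that.

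The cost is wording only. The statistical price is about 1-2 points of power against the unadjusted model if therapist and site variance are both near zero.

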### Analysis of secondary outcomes

Secondary outcomes include the cost-effectiveness of art psychotherapy (EQ-5D-3L and ReQoL-UI), longitudinal changes in aggressive behavior (weekly MOAS score) and changes in patient distress relating to psychiatric symptoms (BSI PSDI). The distribution of the secondary outcomes will be assessed graphically using histograms and boxplots. Depending on the score distributions, the mean (SD) or median [IQR] will be tabulated overall and by trial arm (art psychotherapy versus usual care).

For the longitudinal changes in aggressive behavior using the weekly MOAS score from week 19 to week 38, the changes will be graphically explored by plotting the mean weekly MOAS scores. As an exploratory analysis, a repeated measures ANCOVA model will be fitted which will include treatment group and the baseline value as the independent variables, and with the weekly MOAS score as the dependent variable. Analyses will be adjusted for stratification based on sex and diagnosis of psychosis.

Further secondary outcomes analyses will be performed as ITT analyses. The secondary outcomes of EQ-5D-3L, ReQoL-10 and BSI PDSI will be recorded at three time points (baseline, 19 and 38 weeks post randomisation). We will use separate linear mixed-effect models with week 19 and 38 scores (EQ-5D-3L, ReQoL-10 and BSI PDSI) as the dependent variables and the interaction of randomisation group with time (week 19, week 38) as the independent variable, adjusted for relevant baseline scores, random effect of the variable indexing strata based on gender and diagnosis of psychosis, and a random effect of clustering (by therapist). We will present the estimated difference in EQ-5D-3L/ReQoL-10/BSI PDSI scores at week 19 and 38 for the intervention group compared to the control group with 95% CI.

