#### Secondary objectives

To determine if interpersonal art psychotherapy is cost-effective compared to usual care.To explore patient characteristics and psychotherapeutic processes/mechanisms within interpersonal art psychotherapy that are influential to treatment.To explore the longitudinal changes in aggressive behaviour after receiving art psychotherapy.To evaluate changes in patient distress related to psychiatric symptoms.

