### Primary outcome

The primary outcome is the frequency and severity of aggressive incidents as measured by the Modified Overt Aggression Scale (MOAS) at week 19 post-randomisation.

The MOAS is completed by a research nurse or clinical support officer at baseline (prior to randomisation), and weekly from week 19 to week 38 post-randomisation, and if necessary, checking with a member of the ward team to ensure that it accurately reflects the participant’s behaviour. The MOAS is not always completed by the same research nurse/clinical support officer, so we are recording who has conducted each assessment.

The MOAS is a validated observer-rated measure that assesses the frequency and severity of aggressive incidents among people with ID over the past week (ICC = 0.93 [16]). The scale consists of four categories: verbal aggression, aggression against property, auto-aggression (against self), and physical aggression (against others). Each category will be scored using a 5-point scale (0 = no events within that category, 4 = most severe form of aggression within the category). The rater selects as many items as are appropriate. The items in each category are summed. The summed scores are multiplied by the severity weight for that category (verbal aggression × 1, aggression against property × 2, auto-aggression × 3, physical aggression × 4). The weighted scores are summed to obtain the total MOAS score, with a higher score indicating more aggressive behavior [16]. Thus, the primary outcome is a change in the MOAS score from baseline to week 19 post-randomisation.

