Unit costs will be sourced for the more recent year available at the time of attaching unit costs to the resource use data (e.g. 2024/2025) with costs prior to this year inflated using an appropriate inflation index (e.g. NHS Cost Inflation Index) [25].

The costing perspective will be that of the NHS, given the limited range of external services available or required to those within secure care. A societal perspective is not considered a relevant secondary analysis for these trial participants. The frequency/severity of aggressive incidents as measured by the MOAS (as described above) at week 38 post-randomisation.2.Longitudinal changes in aggressive behaviour are assessed weekly between 19 and 38 weeks post-randomisation using the MOAS score (as described above).3.Patient distress attributed to psychiatric symptoms is assessed at baseline, 19 and 38 weeks post-randomisation using the Brief Symptom Inventory (BSI) Positive Symptom Distress Index (PSDI).

The Brief Symptom Inventory (BSI) is a 53-item self-report instrument designed to assess psychological symptoms over the past week. The BSI is composed of nine primary symptom dimensions (somatization, obsessive–compulsive, interpersonal sensitivity, depression, anxiety, hostility, phobic anxiety, paranoid ideation, and psychoticism). Participants rate the extent to which a specific problem has distressed them in the past 7 days, using a 5-point scale (0 = not at all to 4 = extremely). Scores are determined by summing values for each symptom dimension and then dividing by the number of items in the respective dimension. The Positive Symptom Total (PST) is the number of items with a positive (nonzero) response and the Positive Symptom Distress Index (PSDI) is the sum of the values with positive responses divided by the PST. Raw scores can be converted to standardised *T* scores, generating a profile that graphically illustrates a respondent’s current psychological symptom presentation [17]. The BSI PSDI is recorded at baseline, 19 and 38 weeks to assess changes in patient distress attributed to psychiatric symptoms.

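### The weekly MOAS model lists no week or arm-by-week term, so it yields an average arm difference over weeks 19 to 38 and no estimate of longitudinal change or of the week-38 difference

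*Protocol article*

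**What the plan says.** Under Secondary objectives, the Protocol article sets the aim "To explore the longitudinal changes in aggressive behaviour after receiving art psychotherapy". The list of secondary outcomes, which runs on at the end of Healthcare resource use and costs, names MOAS at week 38 as one outcome. It then names a second: "Longitudinal changes in aggressive behaviour are assessed weekly between 19 and 38 weeks post-randomisation using the MOAS score". Under Primary outcome, the MOAS is scheduled at baseline and "weekly from week 19 to week 38 post-randomisation".

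Analysis of secondary outcomes plans a plot of mean weekly scores and one model: "As an exploratory analysis, a repeated measures ANCOVA model will be fitted". Its explanatory terms are stated ("a repeated measures ANCOVA model will be fitted which will include treatment group and the baseline value as the independent variables"), as is its response ("with the weekly MOAS score as the dependent variable"). The only further term is "Analyses will be adjusted for stratification based on sex and diagnosis of psychosis".

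The next paragraph of that section covers EQ-5D-3L, ReQoL-10 and BSI PSDI. Those models have "the interaction of randomisation group with time (week 19, week 38) as the independent variable", together with baseline, strata and a therapist random effect, and arm differences at weeks 19 and 38 are promised with 95% CIs.

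**The concern.** The objective and the outcome are about change over the follow-up period. The listed terms describe a model in which the arm effect does not depend on the week. Such a model answers whether the arms differ on average between weeks 19 and 38. It does not say whether a difference present at the end of treatment is kept, lost or still building.

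Week-38 MOAS is affected as well. It is listed as an outcome in its own right, but no model under Analysis of secondary outcomes is said to produce its arm difference.

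At stake is the inferential use of about 20 scores per participant. Two analysts following the text could also fit different models, one reading time into the model's name and one fitting only the listed terms, and both could claim to have followed the plan.

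**Working it through.** **Plan's own figure.** The plan states no figure for this analysis. The 59 per arm used below comes from Sample size. It reproduces from a 5-point difference, SD 10, baseline correlation 0.25, two-sided 5% alpha and 80% power, but the point does not depend on it.

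**Step 1: the terms side by side.**

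| Outcome | Follow-up times | Arm | Time | Arm-by-time | Contrast named |
|---|---|---|---|---|---|
| EQ-5D-3L, ReQoL-10, BSI PSDI | 2 (weeks 19, 38) | yes | yes | yes | differences at weeks 19 and 38 |
| Weekly MOAS | 38 − 19 + 1 = 20 | yes | not listed | not listed | none |

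**Step 2: what the listed terms estimate.** Write the true arm difference in week t as d(t). With the same weeks observed for everyone, the arm coefficient in a model with arm, baseline and strata only targets the mean of d(t) over the 20 weeks. Four illustrative linear courses follow. The 5 points is the plan's minimum clinically important difference, and slope = (last − first)/19.

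| Course of d(t) | Mean over 20 weeks | Slope per week | Difference at week 38 |
|---|---|---|---|
| constant −2.5 | −2.5 | 0 | −2.5 |
| fading, −5 to 0 | (−5 + 0)/2 = −2.5 | 5/19 = +0.263 | 0 |
| growing, 0 to −5 | (0 − 5)/2 = −2.5 | −5/19 = −0.263 | −5 |
| crossing, −5 to +5 | (−5 + 5)/2 = 0 | 10/19 = +0.526 | +5 |

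The first three have the same mean, while their week-38 differences range from 0 to −5.

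**Step 3: check on simulated data.** One simulated draw, with the same random numbers reused for each course: 59 per arm, 20 complete weeks, baseline SD 10 with coefficient 0.25, person SD 6 and residual SD 7.5. The last two are assumptions. They imply a weekly SD of √(0.25² × 10² + 6² + 7.5²) = √98.5 = 9.9, close to the plan's 10. A random-intercept model was fitted with and without week and arm-by-week.

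| Course | Arm coefficient, listed terms only | Arm-by-week estimate (SE 0.054) | True slope |
|---|---|---|---|
| constant | −3.73 | +0.010 | 0 |
| fading | −3.73 | +0.273 | +0.263 |
| growing | −3.73 | −0.253 | −0.263 |
| crossing | −1.23 | +0.536 | +0.526 |

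The gap between −3.73 and the true −2.5 is chance in this one draw, and it shifts every row equally (−1.23 against a true 0). What matters is that the first three rows are identical on the listed terms and separate once arm-by-week is added. The SE is illustrative: random slopes or serial correlation would change it.

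**Step 4: is the time course or week 38 estimated elsewhere?** The plot of weekly means is descriptive. The reliable-change classification under Subgroup analyses runs from baseline to week 38 and is repeated for MOAS, but it is set up for therapy completers and does not compare the randomised arms at week 38. No other planned analysis was found that gives a between-arm estimate of either quantity.

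**The case against.** The strongest reply is that a repeated measures ANCOVA, in its classical form, carries occasion as the within-person factor, usually with group-by-occasion. The sentence may list only the between-person variables and leave time to the model's name. This stands in part: the text does not prove that time will be left out. It does not remove the problem, because the plan lists the terms, time is not among them, and no contrast is named. The next paragraph shows that the interaction was written out where it was wanted.

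It is also fair that the objective is only to explore, that the model is labelled exploratory, and that weekly means will be plotted. A reader might infer that the trial could report no time course at all. The plot shows that this goes too far. What is missing is an estimate with its uncertainty.

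A reader might also infer that anyone with a missed week would be dropped, against the intention-to-treat principle. The document does not support this. It names no fitting method and gives no rate of missed weeks, and Sensitivity analyses plans imputation of secondary outcomes, though only as a sensitivity analysis. The classical form that needs complete records is also the one that contains time, so that charge cannot be combined with the charge that time is absent.

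**Conclusion.** The point holds as a defect in the stated model. On the terms listed, the weekly MOAS analysis estimates an average arm difference over weeks 19 to 38. It gives no between-arm estimate of longitudinal change and none for week-38 MOAS. In the illustration, courses whose week-38 differences span the plan's full 5-point clinically important difference return the same arm coefficient.

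This rests on taking the term list as complete. If time is meant to be implicit in the model's name, the defect is an unstated term and contrast, and the correction is the same. The linear courses and variance components are assumptions used only for illustration. The consequence is confined to one secondary objective and one secondary outcome; the week-19 primary analysis is not touched. It is worth correcting before the analysis is run.

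**What to change.** Replace the repeated measures ANCOVA for weekly MOAS with a likelihood-based linear mixed model fitted to all available weekly scores from week 19 to week 38. State its terms: arm, week, arm-by-week, baseline MOAS, the strata, and the same therapist clustering term as the other repeated outcomes. Decide in advance whether week is categorical or linear, and name the within-person covariance, for example a participant random intercept and slope, or AR(1) residuals. A fully unstructured matrix for 20 occasions would need 20 × 21/2 = 210 parameters. Report the arm-by-week contrast (the slope difference if week is linear; the change in arm difference from week 19 to week 38 if it is categorical) and the model-based arm difference at week 38, each with a 95% CI. Keep the plot of weekly means.

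The cost is plan wording only, with the same data and the same software. Statistically it adds 2 fixed effects if week is linear, or 19 + 19 = 38 if categorical, plus the covariance parameters. Linear week is cheaper but assumes a straight line over the period. The analysis can remain exploratory.
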